***Zarit Burden Interview-12 item***

| Do you feel/wish… | Never | Rarely | Sometimes | Quite frequently | Nearly always |
| --- | --- | --- | --- | --- | --- |
| 1. You don’t have enough time for yourself? | 0 | 1 | 2 | 3 | 4 |
| 1. Stressed between caring and meeting other responsibilities? | 0 | 1 | 2 | 3 | 4 |
| 1. Angry when around your relative? | 0 | 1 | 2 | 3 | 4 |
| 1. Your relative affects your relationship with others in a negative way? | 0 | 1 | 2 | 3 | 4 |
| 1. Strained when you are around your relative? | 0 | 1 | 2 | 3 | 4 |
| 1. Your health has suffered because of your involvement with your relative? | 0 | 1 | 2 | 3 | 4 |
| 1. You don’t have as much privacy as you would like, because of your relative? | 0 | 1 | 2 | 3 | 4 |
| 1. Your social life has suffered because you are caring for your relative? | 0 | 1 | 2 | 3 | 4 |
| 1. You have lost control of your life since your relative’s illness?? | 0 | 1 | 2 | 3 | 4 |
| 1. Understanding about what to do about your relative | 0 | 1 | 2 | 3 | 4 |
| 1. You should be doing more for your relative? | 0 | 1 | 2 | 3 | 4 |
| 1. You could do a better job in caring for your relative? | 0 | 1 | 2 | 3 | 4 |

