## **Aim 1: EDITH-HC Training and Tool Development**

**Educational Videos.** We will develop and refine 5, 5-10 minute videos, addressing topics or challenges FCPs frequently encounter in dementia caregiving at EOL, including, but not limited to, knowing what to expect as dementia progresses (Video 1), feeding as EOL approaches (Video 2), and symptom management (Video 3); and instructions on how to use the assessment tool (Video 4) and complete the care partner burden assessment embedded in the hospice’s electronic health record (EHR) (Video 5). Video content will draw upon literature review and information from prior interviews with clinicians and FCP. We will receive feedback on the videos from Black and white FCP, clinicians, and research/content experts using a modified Delphi approach incorporating user-centered design protocol (below). Videos will contain relevant information, strategies for addressing FCP challenges, and a case study to which clinicians can apply information and strategies. Providing the training in a video format will allow clinicians to complete the training at their convenience or as in-service modules, reducing burden. We will take steps to have the training count as continuing education units. Additional video topics may be developed depending on the needs of the clinicians and FCP.

**Assessment Tool.** We will develop and refine an assessment checklist adapted from a previously validated dementia caregiving burden assessment tool that focuses on and incorporates care partner burden and challenges specific to the home hospice setting. To limit burden on clinicians and FCP, the tool will provide clinicians with a series of prompts and strategies to address FCP problems identified using the assessment tool. The tool will support clinicians and FCP to identify multiple strategies for addressing issues, decide which strategy will be most effective, and devise a plan to implement the most effective strategy. The tool will be designed so that it can complement and be incorporated into standard hospice care planning. Clinicians will be trained to use the assessment tool in an educational video (previous section). We will receive feedback on the tool from Black and white FCP, clinicians, and research/content experts using a user-centered design protocol (below).

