
**Intervention.** Clinicians in the intervention group will have access to the training and assessment tool. The training may be delivered as part of a team in-service or other meeting or clinicians may access it on their own time. If the latter, they will be asked to complete the modules within 2 weeks of access being granted. They will be asked to use the assessment tool with Black and white FCP of home hospice PLwD who will be enrolled in the study by research study team members. The tool will be used during regularly scheduled visits to the patient and at up to 3 subsequent visits. Clinicians will be provided with copies of the assessment tool to complete with FCP during visits. FCP will continue to receive standard home hospice care in addition to the intervention.

**Standard Care Control.** FCP in the standard care control group will receive home hospice services as usual. These FCP will complete the same measures as participants in the intervention condition on the same timeline using identical assessment procedures.

**Hypotheses.** >70% of clinicians will 1) complete the training, 2) use the tool as intended, 3) report the training and tool are useful, and 4) report satisfaction with the training and tool. Compared to usual care: *Feasibility/acceptability:* Clinicians who complete the training and use the tool (intervention group) will have greater knowledge of dementia-related challenges in EOL care and how to manage them. Those in the intervention group will report it helps them identify individual PLwD and FCP challenges and suggest appropriate management strategies. *Primary outcome:* FCP in the intervention group will report reduced FCP burden. *Exploratory outcomes:* FCP of intervention group will experience greater self-efficacy and preparedness. PLwD of intervention group clinicians will experience increased utilization of hospice interdisciplinary team (IDT) member services and lower rates of hospice disenrollment. Exploratory analyses will examine racial disparities in FCP burden and PLwD disenrollment.

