**Quantitative Analysis.** We will calculate descriptive statistics to characterize the sample of participants in each aim. **Aim 3.** We will calculate changes in participant outcomes by comparing individual responses to questions at baseline and various points in time after exposure to the training and tool. To establish preliminary efficacy, we use a continuous measure of FCP burden using the 12-item Zarit Burden Interview (ZBI). The primary analysis will be a full information mixed model approach. We base primary power calculations on a more conservative two-group comparison of endpoint means (differences in means) with possible attrition. We assumed σ (variance)=9.8 (for the ZBI), α=0.05 R (reliability)=0.9 and g=2 groups (intervention and usual care). We estimated the variance inflation factor from the design effect of clustering within clinician: Vif=1+(Nc-1)Icc=1.09 (with cluster size, Nc=4 patients per provider) and intracluster correlation coefficient (Icc=0.03). Assumptions are based on earlier care partner studies in racial/ethnic minority samples. Assuming power of 0.80, with 80 per group, we would be able to detect a moderate effect size (Cohen’s d89=0.49), equivalent to ~4.80 points on the ZBI. We also examined sample size requirements for the detection of other endpoint differences: 4.0, 4.5, and 5 points on the ZBI. We examined different scenarios regarding correlations between baseline and follow-up outcome measures. We modified the formula from Fleiss (p 4-5) to include different scenarios related to correlations between the two waves of data: n*= [4(1-ρ)(σ2)(Zα/2+Zβ)2] / δ2 adjusting for unreliability: n=(n*Vif) / R.

The power calculation is based on a sample of 48 care partners and 4 care partners per clinician, and ρ (correlations between repeat measures of each person in waves of data)=0.5, 0.6 and 0.7, the resulting estimates of minimal detectable intervention arm differences are δ=6.21, 5.56, and 4.81 for ZBI, thus demonstrating that a medium effect size (Cohen’s d=0.49 to 0.63) could be detected with this sample size. As the study progresses, actual enrollment may change and analyses will be adjusted accordingly.

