***Clinicians***

1. How often have you used any of the information in the educational videos in your work with home hospice patients with dementia and their families?

□ Frequently: with most of my patients with dementia

□ Sometimes: with some of my patients with dementia

□ Rarely: with a few of my patients with dementia

□ Never: I have not applied any of the information from the videos in my clinical practice

1. I used the information in the educational videos with home hospice patients without dementia:]

□ Yes

□ No

1. Which parts of the educational videos did you use in your clinical practice (check all that apply)?

□ Main point of video 1

□ Main point of video 2

□ Main point of video 3

□ Main point of video 4

□ Other (specify):

1. Overall, how satisfied are you with the educational videos?
   1. Very dissatisfied
   2. Dissatisfied
   3. Neutral
   4. Satisfied
   5. Very Satisfied
2. With how many FCP did you use the [assessment tool/worksheet]?

0 1 2 3 4 >4

□ I don’t have any patients with dementia on my caseload.

1. About how long did it take you to use the [assessment tool/worksheet] with a family member for the first time?

minutes

1. About how long did it take you to use the [assessment tool/worksheet] with a family member during follow-up visits?

minutes

1. How helpful was the [assessment tool/worksheet] when working with family members?
   1. Not at all helpful
   2. Slightly helpful
   3. Moderately helpful
   4. Helpful
   5. Very Helpful

7a. What about the [assessment tool/worksheet] did you find helpful when using with family members?

7b. What about the [assessment tool/worksheet] did you find least helpful when using with family members?

1. How difficult was it to use the [assessment tool/worksheet] as part of your clinical practice? (reverse code)
   1. Very difficult
   2. Difficult
   3. Moderately difficult
   4. Slightly difficult
   5. Not at all difficult

9a. What about the [assessment tool/worksheet] was easy to use?

9b. What about the [assessment tool/worksheet] made it difficult to use?

1. Overall, how many times did you use the worksheet with each family member?
   1. 4 times
   2. 1- 3 times
   3. Not at all
2. You were asked to use the worksheet up to four times with each family member enrolled in the study. Did you find that to be
   1. Not enough times
   2. The right amount of times
   3. Too many times

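### Item 10 of the primary-outcome burden scale is printed as a favourable state on burden codes with no reverse-scoring note; fielded and summed as printed, it would tend to attenuate a benefit

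*Protocol*

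**What the plan says.** Section 9 (Analytic Methods) names the efficacy measure: "we use a continuous measure of FCP burden using the 12-item Zarit Burden Interview (ZBI". The Aim 3 hypotheses fix the direction of benefit: "FCP in the intervention group will report reduced FCP burden". Under Aim 3, burden is collected at baseline and after each of three clinician follow-up visits.

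The Appendix prints the scale with one stem and one set of response columns for all items: "Do you feel/wish… | Never | Rarely | Sometimes | Quite frequently | Nearly always", coded 0 to 4. A typical row is "You have lost control of your life since your relative’s illness", where a higher code plainly means more burden. Item 10 reads "Understanding about what to do about your relative" with the same codes. No scoring instruction accompanies the scale.

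Elsewhere the Appendix does record scoring direction. One clinician item is marked: "How difficult was it to use the [assessment tool/worksheet] as part of your clinical practice? (reverse code". The dementia knowledge scale has step-by-step recoding rules.

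The intervention works on what care partners do about their problems. Of the assessment tool, the Aim 1 section says: "The tool will support clinicians and FCP to identify multiple strategies for addressing issues", then "decide which strategy will be most effective, and devise a plan to implement the most effective strategy".

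**The concern.** Read with 'feel', a care partner who nearly always understands what to do scores 4 on item 10, the maximum burden code, and one who never does scores 0. Every other row runs the opposite way. A plain sum would then count an improvement on this row as added burden. Baseline adjustment would not remove the error, because the wrong sign acts on the change as well as on the level.

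The row is also close to what the tool sets out to improve, namely finding strategies and choosing among them. Section 9 says the pilot should establish preliminary efficacy, collect normative data and help identify the outcome for a fully powered trial. A faulty item would therefore carry into the effect estimate and the reference values that the later trial is built on.

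**Working it through.** **1. Direction of the rows.** Items 1 to 9 describe strain or loss (time, stress, anger, relationships, health, privacy, social life, control). Items 11 and 12 describe falling short as a carer. For these eleven, higher means worse. Item 10 is the only favourable state. The scale maximum is 12 × 4 = 48, and item 10 can move the total by 4 points in the wrong direction.

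**2. Reproducing the plan's power figures.** Inputs from Section 9: 9.8 for the ZBI (labelled a variance, but the figures reproduce only if it is used as an SD), two-sided α = 0.05, power 0.80, R = 0.9, Vif = 1 + (4 − 1) × 0.03 = 1.09, and 48 care partners, taken as per arm.

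Formula: n = [4(1 − ρ) × 9.8² × (1.960 + 0.842)² / δ²] × 1.09 / 0.9.

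Power: Φ(d / (s√(2/48)) − 1.96), with s = 9.8 × √(2(1 − ρ) × 1.09 / 0.9).

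The stated differences imply n of 47.3, 47.3 and 47.4 against 48, so the plan's figures reproduce.

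**3. Effect of the item as printed.** Suppose the intervention improves item 10 by x points. A burden-keyed item would contribute −x; the printed item, read with 'feel' and summed, contributes +x. The measured benefit is 2x too small.

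With an even spread (assumption), x = δ/12, so the measured effect is δ − 2δ/12 = (10/12)δ. The SD and R are held at the plan's values.

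| ρ | Stated δ | Power at 48 per arm | (10/12)δ | Power | n per arm for 80% |
|---|---|---|---|---|---|
| 0.5 | 6.21 | 80.5% | 5.175 | 65.2% | 69 |
| 0.6 | 5.56 | 80.6% | 4.633 | 65.3% | 69 |
| 0.7 | 4.81 | 80.5% | 4.008 | 65.2% | 69 |

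Worked for ρ = 0.5: s = 10.785 and the standard error is 10.785 × √(2/48) = 2.20. Then 6.21/2.20 − 1.96 ≈ 0.86 gives 80.5%, and 5.175/2.20 − 1.96 ≈ 0.39 gives 65.2%.

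**4. Range over x**, with the correctly keyed benefit held at the stated δ.

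| x | Points lost (2x) | Power at ρ = 0.5 / 0.6 / 0.7 |
|---|---|---|
| 0.25 | 0.5 | 74% / 73% / 72% |
| 0.5 | 1.0 | 66% / 64% / 61% |
| 1 | 2.0 | 48% / 44% / 38% |

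For scale, an even share of the stated differences is 4.81/12 = 0.40 to 6.21/12 = 0.52 points per item. The x = 1 row therefore assumes about 2 to 2.5 times the average item effect.

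**5. The prorated 11-item score.** Under an even spread, eleven items carry 11δ/12, and prorating by 12/11 returns δ. The expected effect is restored without relying on how item 10 was understood.

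**The case against.** The strongest case against the point is that the protocol does not show the error reaching the analysis.

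- **Scoring.** No ZBI total-score rule is stated. Item recoding commonly sits in a statistical analysis plan or data dictionary, which is not at hand, and its absence here is no fault. A missing mark is also weak evidence. The clinicians' difficulty question is marked for reverse coding, while the care partners' parallel question with the same five options is not.
- **Reading.** The stem offers 'feel' or 'wish'. A respondent who wishes for understanding about what to do reports an unmet need, which is the burden direction. Item 12 also reads naturally with 'wish'.
- **Fielding.** Item 10 is the only row without a question mark, two items of the preparedness scale are printed twice, and item 8 of the self-efficacy scale lacks the lead-in of the other seven. This may be a copying slip in the Appendix. Data are collected by phone or electronic survey, so the wording actually used is not shown.

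These arguments stand against a stronger reading that a reader might infer: that the primary outcome is definitely biased against the intervention. The documents support that only if the item is fielded as printed, read with 'feel' and summed unreversed. A reader might also take the loss to be 32% to 42% of the detectable difference (2/6.21 and 2/4.81). That needs a full one-category mean shift on this single item, for which the protocol gives no basis. Nor does a reversed effect follow: with one item in twelve affected, that would require the benefit to be concentrated in item 10.

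The arguments do not remove the point itself. The printed row conflicts with the direction of its own scale, and later recoding cannot repair wording that respondents may have read in two ways.

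**Conclusion.** The point holds as an instrument-text error in the primary outcome with a conditional consequence. If the form is used and summed as printed, item 10 is mis-keyed under 'feel' or noisy under 'wish', and it would tend to shrink a real benefit. The illustrative size is a 2/12 = 17% loss of measured effect and a fall in power from about 80% to about 65% at 48 per arm. This rests on an even spread of effect, the 'feel' reading, no recoding, and the plan's SD and reliability unchanged. Any loss of scale reliability is plausible but cannot be quantified from the protocol. Should-fix, moderate confidence: the check is cheap and the scale is primary, but this is a pilot and neither the fielded wording nor the scoring is shown.

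**What to change.** 1. Check item 10, in the Appendix and in the fielded phone and electronic forms, against the source instrument. Correct it so that a higher score means more burden, before further data are collected. The protocol does not give the source wording, so the correction must be taken from the instrument and not guessed.
2. Record with a version flag which wording each participant received at each assessment.
3. For forms completed with the printed wording, use the 11 unaffected items prorated to 12 in the primary total.
4. Report scoring item 10 as 4 minus the response only as a sensitivity analysis, and only if it is confirmed that respondents read the item with 'feel'. Under the 'wish' reading, that recode would create the error it is meant to remove.

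The cost is a minor amendment, a version flag, a scoring line and a small loss of comparability between versions. The 11-item score also gives up any real effect that is specific to item 10.

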# Aim 3. Electronic Health Record Data (post intervention, intervention and control)

1. Patient age, gender, race/ethnicity, and whether dementia is a primary or comorbid diagnosis
2. Dates of hospice enrollment and discharge
3. Hospice discharge status
4. Dates of hospice clinician visits
5. Clinician visits (e.g. physician, nurse, social worker; study participants will be identified by study identifier)
6. Duration of hospice clinician visits
7. Dates of care partner burden assessments
8. Clinician making burden assessment (e.g. physician, nurse, social worker; study participants will be identified by study identifier)
9. Care partner burden assessment scores
